#### Subsequent study visits and later outcomes

Subsequent study visits, where possible, will coincide with routine outpatient appointments. If the recipient is an inpatient, assessment will be made in hospital where appropriate. The study visits will occur on the following dates:Study visit 2—Day 30 (± 2 weeks)Study visit 3—Month 3 (± 1 month)Study visit 4—Month 6 (± 1 month)

The outcome assessments for each study visit are summarised in Table 4.

**Table 4 Tab4:** Study outcome measures and participant visits

Endpoint measure	**Inpatient stay** **Study visit 1**	**Day 30 (± 2 weeks)** **Study visit 2**	**Month 3 (± 1 month)** **Study visit 3**	**Month 6 (± 1 month)** **Study visit 4**
Biochemical	Days 1–7: • Bilirubin (μmol/L) • GGT (IU/L) • AST (IU/L)/ALT (IU/L) • INR • ALP (IU/L) • Urea (mmol/L) • Creatinine (μmol/L) • Lactate (HDU/ITU) Days 1–3: • MEAF score	• Bilirubin (μmol/L) • GGT (IU/L) • AST (IU/L)/ALT (IU/L) • INR • ALP (IU/L) • Urea (mmol/L) • Creatinine (μmol/L)	• Bilirubin (μmol/L) • GGT (IU/L) • AST (IU/L)/ALT (IU/L) • INR • ALP (IU/L) • Urea (mmol/L) • Creatinine (μmol/L)	• Bilirubin (μmol/L) • GGT (IU/L) • AST (IU/L)/ALT (IU/L) • INR • ALP (IU/L) • Urea (mmol/L) • Creatinine (μmol/L)
cfDNA	Days 1, 3, 7, 14 or date of discharge	Sample to be taken with routine bloods	Sample to be taken with routine bloods	Sample to be taken with routine bloods
Peri-operative and survival	• Length of stay in (ITU/HDU) (days) • Total length of hospital stay (days) • Requirement for renal replacement therapy • Graft and patient survival at day 7 post-transplant • Primary non-function	• Graft and patient survival at day 30 post-transplant • Requirement for renal replacement therapy (HD, HF, HDF, PD) at any time	• Graft and patient survival at month 3 post-transplant • Requirement for renal replacement therapy (HD, HF, HDF, PD) at any time	• Graft and patient survival at month 6 post-transplant • Protocol MRI Scan (depending on site capacity) • Requirement for renal replacement therapy (HD, HF, HDF, PD) at any time
Safety	• Recipient infection^a^ • Clinically suspected treated rejection • Biopsy-proven acute rejection • Biliary complications^b (i-ii)^ • Vascular complications^c (i-vi)^ • Reoperation rate • Technical complications and device failures • Any other reported adverse event	• Recipient infection^a^ • Biopsy-proven acute rejection • Biliary complications^b (i-ii)^ • Vascular complications^c (i-vi)^ • Reoperation rate • Technical complications and device failures • Any other reported adverse event	• Recipient infection (CMV infection, fungal infection, post-operative sepsis) • Biopsy-proven acute rejection episodes • Biliary complications^b (i-ii)^ • Vascular complications^c (i-vi)^ • Reoperation rate • Technical complications and device failures • Any other reported adverse event	• Recipient infection (CMV infection, fungal infection, post-operative sepsis) • Biopsy-proven acute rejection episodes • Biliary complications^b (i)^ • Vascular complications^c (i-vi)^ • Reoperation rate • Technical complications and device failures • Any other reported adverse event
Immunosuppression	Immunosuppression regimen at day 7 (including doses)	Immunosuppression regimen at day 30 (including doses)	Immunosuppression regimen at month 3 (including doses)	Immunosuppression regimen at month 6 (including doses)

^a^Infection, defined as both clinically diagnosed treated infection and infection with a positive microbiological culture result

^b^Biliary complications diagnosed radiologically, e.g. a non-protocol MRI or CT scan in clinically symptomatic patient: (i) biliary strictures—anastomotic and non-anastomotic. Defined as those requiring surgical or radiological intervention and (ii) bile duct leaks. Defined as those requiring drainage, refashioning of anastomosis or stenting

^c^Vascular complications including (i) bleeding, defined as bleeding requiring transfusion and/or radiological/surgical intervention; (ii) hepatic artery stenosis, defined as causing graft dysfunction requiring radiological or surgical intervention or resulting in graft loss; (iii) hepatic artery thrombosis, defined as formation of new clot resulting in graft dysfunction or loss, or requiring pharmacological, radiological or surgical intervention; (iv) portal vein thrombosis, defined as formation of new clot resulting in graft dysfunction or loss, or requiring pharmacological, radiological or surgical intervention, (v) portal vein stenosis, defined as causing graft dysfunction requiring radiological or surgical intervention or resulting in graft loss and (vi) IVC/hepatic vein occlusion, defined as formation of new clot resulting in graft dysfunction or loss, or requiring pharmacological, radiological or surgical intervention

Whilst the endpoint for trial participation will be 6 months, patients will also be consented for ongoing follow-up (12 months) by linkage to outcomes recorded by in the NHSBT transplant registry. This will allow the ongoing assessment of resource use (hospital stay and reasons for re-admission), biochemistry results (liver and renal function), transplant-related renal dysfunction and longer-term patient/graft survival.

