#### Secondary outcome measures

ClinicalProportion of livers transplanted in the two armsLiMAx (maximum liver function capacity) test performed after 1 h of liver stabilisation during NMP, repeated at 5 h and subsequently every 6 h till end of perfusion where feasible. If the decision to transplant has been made by 6 h of NMP, the test will not be repeated. The LiMAx test will allow real-time monitoring of CYP1A2 (prominent in functional livers cells and less prominent in damaged cells) and is based on the metabolism of ^13^C-methacetin. This will enable measurement of liver capacity and functional reserve during perfusion [60].Cell-free DNA (cfDNA) measured at baseline (pre-NMP) and during preservation (1, 2, 4 and 6 h and end of perfusion). Further measurements taken from the recipient peri-operatively (before transplant) and re-perfusion (following liver transplantation). Post-operative samples collected on days 1, 3, 7 and 14 (if the patient is discharged prior to day 14—a sample will be collected on the day of discharge instead). Outpatient sample collection will align with clinic visits on day 30 and months 3 and 6. cfDNA has been correlated with allograft injury, rejection and formation of de novo donor-specific antibodies [61].Biochemical liver function in the first 7 days post-transplant: ALT, GGT, INR, bilirubin and peak serum AST (where AST measurements available) in the first 7 days post-transplant. Peak serum AST is a validated surrogate marker, predictive of PNF as well as graft and patient survival [62]. It is also associated with histological evidence of moderate to severe reperfusion injury [63].Model of Early Allograft Function (MEAF) [64]: a score (between 0 and 10) based on bilirubin, INR and ALT within the first three post-operative days.Primary non-function (PNF): irreversible graft dysfunction requiring emergency liver replacement during the first 10 days after liver transplantation, in the absence of technical or immunological causes.Post-reperfusion syndrome (PRS) [65]: a decrease in mean arterial pressure (MAP) of more than 30% for more than 1 min during the first 5 min after reperfusion [65].Need for renal replacement therapy (haemodialysis, haemofiltration, peritoneal dialysis) during the first 7 days post-operatively.Duration of ITU/HDU and hospital stay.Graft survival (defined as a functioning transplant in the absence of death and re-transplantation) at day 7, day 30, month 3 and month 6.Patient survival at day 7, day 30 and months 3 and month 6. In addition, 12-month clinical outcomes (obtained from NHSBT registry) will also be reported:aGraft and patient survivalbTotal number of days in hospital in the last year (excluding transplant admission)cTotal number of re-admissions for:•Recipient infection•Acute rejection•Chronic rejection•Biliary complications•Vascular complications•Disease recurrence•Other reasonsdTransplant-related renal dysfunctioneBiochemistry (liver and renal function)The following safety information will be recorded:aOrgan discard ratebPerfusate culture. At the end of preservation, a sample will be taken for microbiological culture.cAdverse event rates and severity, graded according to the Clavien–Dindo classification [66] during the first 7 days, day 30, month 3 and month 6:•Recipient infection•Biopsy proven acute rejection•Biliary complications (biliary strictures—anastomotic and non-anastomotic, bile duct leaks)•Vascular complications (bleeding, hepatic artery stenosis, hepatic artery thrombosis, portal vein thrombosis)•Reoperation ratedTechnical complications/device failures

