Safety outcomesRecipient infection (defined as both clinically diagnosed treated infection and infection with a positive microbiological culture result)Clinically suspected treated rejectionBiopsy-proven acute rejection episodesBiliary complications diagnosed radiologically, e.g. a non-protocol MRI or CT scan in clinically symptomatic patient:◦Biliary strictures——anastomotic and non-anastomotic. Defined as those requiring surgical or radiological intervention◦Bile duct leaks. Defined as those requiring drainage, refashioning of anastomosis or stenting.Vascular complications◦Bleeding. Defined as bleeding requiring transfusion and/or radiological/surgical intervention.◦Hepatic artery stenosis. Defined as causing graft dysfunction requiring radiological or surgical intervention or resulting in graft loss.◦Hepatic artery thrombosis. Defined as formation of new clot resulting in graft dysfunction or loss, or requiring pharmacological, radiological or surgical intervention.◦Portal vein thrombosis. Defined as formation of new clot resulting in graft dysfunction or loss, or requiring pharmacological, radiological or surgical intervention.◦Portal vein stenosis. Defined as causing graft dysfunction requiring radiological or surgical intervention or resulting in graft loss.◦IVC/hepatic vein occlusion. Defined as formation of new clot resulting in graft dysfunction or loss, or requiring pharmacological, radiological or surgical intervention.Reoperation rateTechnical complications and device failuresAny other reported adverse event

Severity will be graded according to the Clavien–Dindo classification [66]—*Supplemental *Table 1.

Immunosuppression

Details of induction immunosuppression and maintenance immunosuppression (including doses) at day 7 post-transplant will be recorded.

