#### Anticipated adverse events

As liver transplant recipients, all recruits to the DeFat trial are at high risk of experiencing AEs due to the complexity of their condition. Many of these events are anticipated as a result of the patient’s medical condition and standard treatment received in hospital. We will only document adverse events if in the opinion of the investigator they are likely to be associated with the trial intervention.

All adverse events meeting the definition of serious adverse event will be recorded.

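### Table 4 changes the infection definition after day 30 and drops bile duct leaks at month 6, without explanation and out of step with the safety outcome list

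*Protocol article*

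**What the plan says.** Three places in the protocol article bear on this.

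- **Secondary outcome measures, safety information.** Adverse event rates, graded by Clavien–Dindo, are to be recorded "during the first 7 days, day 30, month 3 and month 6". The list includes recipient infection, with no definition or restriction, and "Biliary complications (biliary strictures—anastomotic and non-anastomotic, bile duct leaks").
- **Safety outcomes, under Inpatient stay.** Infection is "defined as both clinically diagnosed treated infection and infection with a positive microbiological culture result". Biliary complications comprise strictures and leaks, each defined by the need for intervention.
- **Table 4, under Subsequent study visits and later outcomes.** Footnote a repeats the broad definition: "Infection, defined as both clinically diagnosed treated infection and infection with a positive microbiological culture result". It is attached only to the inpatient and day 30 columns. The month 3 and month 6 columns read instead "Recipient infection (CMV infection, fungal infection, post-operative sepsis"). Biliary complications refer to footnote b, items (i) and (ii), at the first three visits, but to item (i), strictures, alone at month 6. The item left out is "ii) bile duct leaks. Defined as those requiring drainage, refashioning of anastomosis or stenting".

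For adverse events in general, the section on Anticipated adverse events says: "We will only document adverse events if in the opinion of the investigator they are likely to be associated with the trial intervention". It exempts serious adverse events, which are all recorded. The section on reporting serious adverse events sets their collection from transplant to 6 months.

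**The concern.** The outcome list names the same events for four time points, and the text sends the reader to Table 4 for what is assessed at each visit. If sites and the electronic case report form follow Table 4, the infection item is not the same variable at day 30 and at month 3, and the month 6 biliary item is narrower than the outcome it is meant to supply. What is not collected at a visit cannot be restored in the analysis.

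Safety is part of the primary objective, and the section on statistical methods puts the weight of the secondary analyses on effect sizes with confidence intervals to inform a later definitive trial. Late infection and biliary rates are among the figures that such a trial would draw on.

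**Working it through.** The documents give no infection or leak rate, so there is no planned figure to reproduce. The check sets the texts side by side.

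| Visit | Outcome list: infection | Table 4: infection | Outcome list: biliary | Table 4: biliary |
|---|---|---|---|---|
| Inpatient stay (first 7 days in the outcome list) | unrestricted | broad (footnote a) | strictures, leaks | strictures, leaks |
| Day 30 | unrestricted | broad (footnote a) | strictures, leaks | strictures, leaks |
| Month 3 | unrestricted | three types | strictures, leaks | strictures, leaks |
| Month 6 | unrestricted | three types | strictures, leaks | strictures only |

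**Span of each gap**, assuming that each visit covers the time since the one before:

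- Infection: the narrower list applies from about month 1 to month 6, so 6 − 1 = 5 of 6 months.
- Leaks: the omission applies from month 3 to month 6, so 6 − 3 = 3 of 6 months.

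**Which events have another route into the data:**

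1. *Late leak.* Footnote b counts only leaks that need drainage, refashioning or stenting. Such a leak would usually meet a criterion in the protocol's definition of a serious adverse event, for example in-patient care or an intervention to prevent serious harm. It is then recorded whatever its cause. Surgical refashioning should also appear under the reoperation rate, which Table 4 lists at month 6. The event is mostly captured, but not under the biliary outcome.
2. *Late serious infection outside the three types.* Captured as a serious adverse event, but not under the infection outcome.
3. *Late non-serious infection outside the three types, treated or culture-positive, judged unrelated.* It falls outside the month 3 and month 6 infection item, and the rule on documenting adverse events excludes it. Table 4 does have a row for any other reported adverse event at every visit, but under that rule nothing requires this event to be reported there. The same infection at day 20 would count.

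The serious adverse event route is also not an equivalent record. The named outcomes are graded by Clavien–Dindo, while the adverse event sections use mild, moderate and severe.

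**Scale.** With at most 30 recipients per arm, one more affected recipient in an arm moves its rate by at least 1/30 = 3.3 percentage points, and by more if fewer than 30 livers are transplanted. This shows how sensitive a rate is to a single event. It does not estimate how many events are missed.

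**The case against.** The best reply is that no text sets the broad infection definition for months 3 and 6. The outcome list gives the time points but does not define infection. The definition in the body of the article sits under the inpatient stay, and footnote a is tied to the first two columns. This stands. A reader might infer that Table 4 contradicts a definition fixed for all four visits; the documents support only an unexplained change of definition between visits. The leak omission is different, because the outcome list names leaks for month 6 and Table 4 does not.

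The second reply is that little is lost, and much of that also stands. Most late leaks and all serious infections remain visible as serious adverse events or reoperations, and the 12-month registry data count re-admissions for infection and for biliary complications. A reader might infer that late leaks go unrecorded altogether; they mostly do not. The clear loss is confined to the third group above.

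It may also be said that the three infection types are meant as examples. The text does not say so, and sites could read it either way.

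Finally, the same table applies to both arms, the primary endpoint is perfusion function at 6 h and is untouched, and little testing of secondary endpoints is planned. Nothing says that rates will be pooled across visits. These points limit the consequence, but they do not reconcile the texts.

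**Conclusion.** The inconsistency is real and modest. The safety outcome list and Table 4 disagree on bile duct leaks at month 6, and Table 4 changes what counts as an infection after day 30 without giving a reason. Followed as written, late non-serious infections outside the three types and judged unrelated are not recorded, and late leaks are not counted under the named biliary outcome.

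The consequence is for the completeness of late safety data and the comparability of rates across visits. A reader might infer a bias between arms; the documents show none, since collection is the same in both. A reader might also suppose that the gap falls in a period of special biliary risk for these grafts; the documents give no timing of such events, and strictures stay listed throughout, with imaging for them at month 6 where site capacity allows.

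The number of missed events cannot be derived. The conclusion assumes that the case report form follows Table 4. If it already uses the broad definition and the full biliary item at every visit, only the article's wording needs correcting.

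**What to change.** Reconcile the Secondary outcome measures, the Safety outcomes list under Inpatient stay, and Table 4:

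- attach footnote a to infection at months 3 and 6, with CMV infection, fungal infection and post-operative sepsis kept as sub-types;
- list both biliary items, strictures and leaks, at month 6;
- make the electronic case report form match.

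If the narrower infection list is intended, say so in the Secondary outcome measures, and report infection by visit without pooling across the two definitions.

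The cost is an edit to the table, a check of the case report form and minor extra data entry at the later visits. Only data recording changes.

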### Sample size {14}

Our preliminary data described above showed that 40% more livers met functional criteria for transplantation where NMP was combined with defatting versus NMP alone (100% vs.60%) [33]. However, this is based on a small sample size and the interventions were tested on a very high-risk group of livers that had all been previously discarded. Using the proposed inclusion criteria, a smaller effect size is anticipated. Whilst the present study is not primarily intended to demonstrate efficacy, a sample size of 60 livers (30 per group) will provide greater than 80% power to detect a difference of 30% (from 65% in the control NMP arm) in those meeting criteria for transplantation (at 5% significance): this is a clinically significant outcome. This sample size should provide sufficient information for the design of a larger, phase III study to formally test the efficacy of the intervention.

### Recruitment {15}

The annual NHSBT report (2018–19) shows that of 735 adult elective liver transplants, 618 (84%) were performed at the participating liver transplant centres [11]. Data from within Eurotransplant show that 23% of livers have moderate to severe steatosis (>30%) on histology [79]. This predicts that 142 livers (annually) and 213 livers (over 18 months) with moderate to severe steatosis would be available at the centres participating in this study. Allowing for a 50% recruitment rate, the recruitment of 60 livers in 18 months is feasible (allowing for small proportion non-steatotic livers to be randomised).

## Assignment of interventions: allocation

### Sequence generation {16a}

If the liver is eligible for the study (at the point of organ inspection by a surgeon from the implanting team at the liver transplant centre) or with results of a clinical biopsy, randomisation will be conducted by the trial co-ordinator (clinical research fellow) who will deliver and be unblinded to the intervention.

Once eligibility is confirmed, the central trial team will use an on-line randomisation service (sealedenvelope.com) to allocate the liver to NMP or NMP with defatting interventions. The allocation sequence will be produced by sealed envelope and quality checked by the trial statistician.

### Concealment mechanism {16b}

Donor organs meeting enrolment criteria will be randomised, using a 1:1 allocation ratio, using permuted blocks of varying undisclosed size and will be stratified by donor organ type (DCD/DBD). The randomisation list will only be accessible to the trial statisticians and sealed envelope. Randomised livers that are not perfused due to unforeseen reasons will not be replaced. It is anticipated that non-perfusion of a randomised liver will be a very uncommon event.

### Implementation {16c}

This is a single-blinded randomised clinical trial. Perfusions will be performed by a member of the central trial team. The trial co-ordinator (clinical research fellow) and/or member of the central trial team will be responsible for randomisation and will be unblinded to the intervention.

## Assignment of interventions: blinding

### Who will be blinded {17a}

After randomisation, setting up the NMP device will follow standard practice, with addition of the apheresis filter and pharmacological protocol. The presence or absence of the lipoprotein apheresis filter will be concealed through the use of a ‘dummy’ filter covered by a drape. This will prevent the local transplant and research team (and therefore the patient) from knowing the study allocation. In the case of a medical emergency or safety concern ascribed to the perfusion, rapid identification of the trial treatment and randomisation code will be permitted and documented.

### Procedure for unblinding if needed {17b}

If urgent unblinding is considered necessary during the liver perfusion, the trial co-ordinator (clinical research fellow) or a member of the central trial team who will be co-ordinating the perfusion and therefore aware of the liver randomisation will disclose allocation to the clinical team. In other circumstances, the PI (or assigned deputy) will request and be given access to the unblinding facility for the individual randomisation through the web-based service (www.sealedenvelope.com). Unblinding of randomisations will be documented along with the reasons triggering them. The individual requesting unblinding at the site will receive an automatic email notification with the arm allocation of the perfused liver. All instances of unblinding should be reported to NHSBT CTU and chief investigator (CI) as soon as possible. Details of the randomisation process and emergency code breaking will be located in the site file. The trial co-ordinator (clinical research fellow) will not be involved in any clinical decision making or any of the study assessments.

